### Ethical Considerations

The Pennington Biomedical Research Center Institutional Review Board approved the study protocol (2021-022-PBRC), and all patients provided written informed consent. All attempts are made to maintain participant privacy and confidentiality. Safeguards such as password-protected computers and networks are in place to limit access to participant data. Study data are labeled with a unique series of letters and numbers. Pennington Biomedical Research Center stores data with this unique identifier. Participants receive up to US $300 for completed participation in the study. This includes compensation of US $50 for completion of visit 1, US $50 for completion of visit 2, and US $125 for completion of visit 3. Participants also receive the wearable device upon completion of the study.

## Results

### Overview

The RESPONSES study has completed participant recruitment (n=60). The flow of participants from screening to enrollment is shown in Figure 2. A total of 1066 potential participants were screened via a web screener for enrollment, and 587 (55.07%) were ineligible for study participation; the most common exclusionary criteria were out-of-range BMI (n=176, 30%) and having a reported income above the cutoff (n=123, 21%). Of the 479 potential participants who were screened via a telephone call, 311 (64.9%) were ineligible owing to exclusionary criteria. Of the 126 potential participants who were eligible after the telephone screener, 48 (38.1%) were food insecure, and 78 (61.9%) were food secure. At screening visits, of the 126 potential participants, a combined 66 (52.4%) were excluded from study participation to reach the target sample size of 60 (47.6%; food-insecure cohort: n=30, 50%; food-secure cohort: n=30, 50%). All data are anticipated to be collected by the end of 2023.

**Figure 2 figure2:**
[figure not shown]
RESPONSES (Effects of Episodic Food Insecurity on Psychological and Physiological Responses in African American Women With Obesity) participant flow diagram.

### Participant Characteristics

Table 2 presents the baseline characteristics of the participants enrolled in the RESPONSES study. On average, participants were aged almost 47 (SD 10.8) years with a mean BMI of 39.6 (SD 5.31) kg/m^2^ at the time of study enrollment. Regarding marital status, 76% (45/59) of the participants were divorced, separated, widowed, or never married. In terms of education level, 58% (35/60) of the participants had a high school diploma, General Educational Development Test certificate, or 1 to 3 years of college. Regarding income, 31% (17/55) of the participants reported an annual income of <US $30,000, and 24% (13/55) reported an annual income of >US $50,000. In terms of employment status, 58% (33/57) of the participants reported being employed full time. The mean poverty-to-income ratio (PIR) among all participants was 1.96 (SD 0.83), whereas the food-insecure cohort reported an average PIR of 2.03 (SD 0.79), and the food-secure cohort reported an average PIR of 1.88 (SD 0.89).

**Table 2 table2:** Baseline characteristics of participants enrolled in the RESPONSES (Effects of Episodic Food Insecurity on Psychological and Physiological Responses in African American Women With Obesity) study.

Characteristics		Food-insecure cohort	Food-secure cohort	Overall
**Age (y)**				
	Participants, n	30	30	60
	Value, mean (SD)	46.93 (10.45)	46.47 (11.32)	46.7 (10.8)
**Weight (kg)**				
	Participants, n	30	30	60
	Value, mean (SD)	106.42 (17.13)	105.82 (14.94)	106.12 (15.94)
**BMI (kg/m^2^)**				
	Participants, n	30	30	60
	Value, mean (SD)	39.31 (5.4)	39.95 (5.29)	39.63 (5.31)
**Waist circumference (cm)**				
	Participants, n	29	30	59
	Value, mean (SD)	114.49 (11.33)	112.9 (10.46)	113.68 (10.83)
**Hip circumference (cm)**				
	Participants, n	29	29	58
	Value, mean (SD)	126.69 (13.87)	126.98 (10.7)	126.84 (12.28)
**Waist to hip ratio**				
	Participants, n	29	29	58
	Value, mean (SD)	0.91 (0.07)	0.89 (0.08)	0.9 (0.07)
**Pulse**				
	Participants, n	29	30	59
	Value, mean (SD)	66.55 (9.65)	67.33 (9.39)	66.95 (9.44)
**Marital status, n/N (%)**				
	Married	5/30 (17)	9/29 (31)	14/59 (24)
	Divorced, separated, widowed, or never married	25/30 (83)	20 (69)	45/59 (76)
**Education, n/N (%)**				
	High school diploma, GED^a^ certificate, or 1-3 y college	20/30 (67)	15/30 (50)	35/60 (58)
	Bachelor’s degree or postgraduate degree	10/30 (33)	15/30 (50)	25/60 (42)
**Annual income (US $), n/N (%)**				
	<30,000	8/29 (28)	9/26 (35)	17/55 (31)
	30,000-39,000	8/29 (28)	5/26 (19)	13/55 (24)
	40,000-49,999	9/29 (31)	3/26 (12)	12/55 (22)
	>50,000	4/29 (14)	9/26 (35)	13/55 (27)
**Household size**				
	Participants, n	29	29	58
	Value, mean (SD)	2.48 (1.48)	3 (1.54)	2.74 (1.52)
**Employment status, n/N (%)**				
	Employed full time (40 h/wk)	16/28 (57)	17/29 (59)	33/57 (58)
	Employed part time	3/28 (11)	3/29 (10)	6/57 (11)
	Unemployed	2/28 (7)	1/29 (3)	3/57 (5)
	Retired	0/28 (0)	4/29 (14)	4/57 (7)
	Medical disability	2/28 (7)	1/29 (3)	3/57 (5)
	Student	0/28 (0)	2/29 (7)	2/57 (4)
	Self-employed, homemaker, or other	3/28 (11)	1/29 (3)	4/57 (7)
	Other	2/28 (7)	0/29 (0)	2/57 (4)
**Financial support, n/N (%)**				
	Family	2/16 (13)	2/10 (20)	4/26 (15)
	Employment	8/16 (50)	5/10 (50)	13/26 (50)
	Government	2/16 (13)	1/10 (10)	3/26 (12)
	Scholarships	2/16 (13)	1/10 (10)	3/26 (12)
	Loans	0/16 (0)	0/10 (0)	0/26 (0)
	Other	2/16 (13)	1/10 (10)	3/26 (12)
**Dependent, n/N (%)**				
	Yes	2/30 (7)	0/30 (0)	2/60 (3)
	No	28/30 (93)	30/30 (100)	58/60 (97)
**Insurance, n/N (%)**				
	None	1/30 (3)	0/30 (0)	1/60 (2)
	Private	16/30 (53)	17/30 (57)	33/60 (55)
	Medicare	4/30 (13)	5/30 (17)	9/60 (15)
	Medicaid	9/30 (30)	8/30 (27)	17/60 (28)
	Use parents’ or legal guardians’ insurance coverage	0/30 (0)	0/30 (0)	0/60 (0)
**Poverty-to-income ratio**				
	Participants, n	28	26	54
	Value, mean (SD)	2.03 (0.79)	1.88 (0.89)	1.96 (0.83)
**Creatinine, n (mean, SD)**				
	Participants, n	30	30	60
	Value, mean (SD)	0.82 (0.21)	0.86 (0.18)	0.84 (0.19)
**Potassium**				
	Participants, n	30	30	60
	Value, mean (SD)	4.23 (0.39)	4.24 (0.37)	4.24 (0.37)
**Uric acid**				
	Participants, n	30	30	60
	Value, mean (SD)	5.49 (1.03)	5.51 (1.06)	5.5 (1.04)
**Calcium**				
	Participants, n	30	30	60
	Value, mean (SD)	9.4 (0.36)	9.39 (0.36)	9.4 (0.36)
**Magnesium**				
	Participants, n	30	30	60
	Value, mean (SD)	2.01 (0.16)	2 (0.21)	2.01 (0.19)
**CPK^b^**				
	Participants, n	30	30	60
	Value, mean (SD)	134.6 (110.47)	148.3 (97.23)	141.45 (103.41)
**ALT^c^**				
	Participants, n	30	30	60
	Value, mean (SD)	19.33 (6.87)	17.33 (0.87)	18.33 (6.42)
**ALK^d^**				
	Participants, n	30	30	60
	Value, mean (SD)	77.93 (27.01)	69.13 (19.78)	73.53 (23.89)
**Iron**				
	Participants, n	30	30	60
	Value, mean (SD)	66.13 (23.08)	62.5 (24.41)	64.32 (23.62)
**Type 1 diabetes, n/N (%)**				
	Yes	2/30 (7)	1/30 (3)	3/30 (5)
	No	28/30 (93)	29/30 (97)	57/30 (95)

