### Aims

The RESPONSES study will address the following aims.

Aim 1: the study will longitudinally assess body weight in addition to psychological and physiological parameters in food-insecure and food-secure African American women with obesity. Body weight is collected to assess the change from week 0 to week 22. Psychological parameters (stress; executive function, decision-making, and motivation; and affect and nonhomeostatic eating) are measured via validated questionnaires. Physiological parameters are measured via 24-hour urine (cortisol) and blood (dehydroepiandrosterone-sulfate [DHEA-S], C-reactive protein [CRP], thyroid hormones, blood glucose, glycated hemoglobin, and insulin) samples as well as an allostatic load total score. These parameters are measured at week 0 and week 22 to examine changes in psychological and physiological mechanisms. We hypothesize that food-insecure African American women with obesity will demonstrate increased body weight and changes in psychological and physiological parameters consistent with elevated stress over 22 weeks compared with food-secure African American women with obesity.Aim 2: the study will examine associations between changes in body weight and psychological and physiological parameters in food-insecure and food-secure African American women with obesity. We are examining associations between (1) change in body weight collected over 22 weeks and change in psychological and physiological parameters collected 22 weeks apart and (2) changes in psychological and physiological parameters.Exploratory aim: the study will longitudinally examine cyclic patterns in body weight, food insecurity, and stress in food-insecure and food-secure African American women with obesity. Body weight is collected daily to assess average weekly change. Food insecurity and stress are assessed weekly via questionnaires. We are examining weekly patterns of body weight, food insecurity, and stress to determine how changes in body weight are related to episodes of food insecurity and stress. Finally, we are assessing mediation analysis of the psychological questionnaires.

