### Outcome Measures and Study Procedures

#### Overview

The primary outcome of the RESPONSES study is the change in *body weight*. The secondary outcomes include *psychological parameters* (stress; executive function, decision-making, and motivation; and affect and nonhomeostatic eating measured via psychological questionnaires) and *physiological parameters* (cortisol, DHEA-S, CRP, thyroid hormones [thyroid-stimulating hormone, free tri-iodothyronine, and free thyroxine], blood glucose, glycated hemoglobin, and insulin levels measured via blood and urine samples, as well as an allostatic load total score). Table 1 summarizes the data collection schedule of study procedures.

**Table 1 table1:** Schedule of RESPONSES (Effects of Episodic Food Insecurity on Psychological and Physiological Responses in African American Women With Obesity) study procedures.

Study procedure		Screening visit	Clinic visit 1 (week 0)	Remote visit 2 (week 11)	Clinic visit 3 (week 22)
Informed consent and HIPAA^a^ authorization		✓			
Health questionnaire and medical history		✓			
Medication inventory		✓			

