### Planned Statistical Analysis

All available daily body weights will be used for analyses. For aim 1, body weight and psychological and physiological parameters will be analyzed using a mixed effects model with time, food security status, baseline BMI, and age. Models will be checked for both normality and heterogeneity of variance in potential subgroups (eg, age and BMI category). Least squares means and tests for differences by food security group will be the primary results. The analysis of aim 2 will focus on correlations among the outcomes from aim 1. Both Spearman and Pearson correlation coefficients will be used to determine the pairwise relationships among outcomes. Depending on the collinearity among outcomes, factor analysis will also be used to explore these relationships. Analysis of the exploratory aim will determine whether the weekly patterns of change in body weight, food security status, and perceived stress are different by food security group and how well these measures are associated with each other over time.

For aim 1, mixed effects models will be used to model psychological and physiological parameters. Furthermore, a linear mixed effects model will be used to model the daily weight over time. In addition to overall changes in body weight between the groups adjusted for BMI, age, and other baseline covariates, smaller temporal changes (ie, weekly) will also be a focus. Modeling these smaller changes should account for the increased fluctuations in the weight of the food-insecure women.

For aim 2, mixed effects models will assess how daily weight change is associated with changes in psychological and physiological parameters. Initial weight, overall weight change, and weekly weight change will all be considered as predictors in addition to more exploratory weight variables, such as the number of days significantly above or below starting weight or average absolute daily weight changes. These variables will be interacted with food security status (group) to determine whether the weight changes have greater effect on food-insecure women.

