**Type 2 diabetes, n/N (%)**				
	Yes	4/30 (13)	8/30 (27)	12/60 (20)
	No	26/30 (87)	22/30 (73)	48/60 (80)

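### Fasting insulin is analysed under one common model with no provision for women who use insulin, although controlled diabetes is admitted and three of the 60 women report type 1

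*Protocol article*

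**What the plan says.** In the protocol article, the exclusion criteria (Textbox 1) remove women with uncontrolled diabetes, defined by a fasting glucose above 250 mg/dL. Controlled diabetes of either type may enter.

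Table 2 shows that it did. The row "Type 1 diabetes, n/N" gives 2 food-insecure women and 1 food-secure woman. The row "Type 2 diabetes, n/N" gives 4 and 8.

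The overview of outcome measures lists among the secondary outcomes "blood glucose, glycated hemoglobin, and insulin levels measured via blood and urine samples, as well as an allostatic load total score". Textbox 2 also makes glycated hemoglobin a component of the allostatic load score.

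Planned Statistical Analysis fixes the aim 1 model: "body weight and psychological and physiological parameters will be analyzed using a mixed effects model with time, food security status, baseline BMI, and age". Further covariates are mentioned only for weight, and are not named: "overall changes in body weight between the groups adjusted for BMI, age, and other baseline covariates". Aim 2 carries the same outcomes into Pearson and Spearman correlations and possibly factor analysis.

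Table 1 schedules the item "Medication inventory" at the screening visit only. The Aims section expects "changes in psychological and physiological parameters consistent with elevated stress over 22 weeks" in the food-insecure cohort compared with the food-secure cohort.

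**The concern.** Fasting insulin is a named outcome whose change is to be read as a metabolic response to food insecurity. In a woman who takes insulin, the measured concentration mixes administered hormone with whatever she secretes herself, so it is not the same quantity as in the other women. The stated model neither sets such women aside nor distinguishes them.

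A main-effect covariate for diabetes would not solve this. It would shift the level for these women but would leave treatment-driven change over 22 weeks, and any extra variance, in the comparison.

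At stake is one secondary outcome in aim 1, and in aim 2 the Pearson correlations that involve insulin. At n = 60, a few extreme values can dominate a Pearson coefficient. The Spearman coefficient limits this, but only for the pairwise results.

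**Working it through.** **1. Table 2 counts.**
- Type 1: (2 + 1)/60 = 5%, which matches the printed percentage. The overall denominators in that row are printed as 30; only 60 fits the 5% and 95%.
- Type 2: (4 + 8)/60 = 20%, as printed.
- Any diabetes: 12/60 = 20% if every woman with type 1 is also in the type 2 row, and 15/60 = 25% if none is.
- By cohort: 4 to 6 of 30 food-insecure (13% to 20%) and 8 to 9 of 30 food-secure (27% to 30%).

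**2. Noise from insulin users in the insulin contrast.** Let u women have a change SD k times that of the others. With 30 per cohort, the standard error of the difference is multiplied by sqrt(((60 − u) + u·k²)/60), however the u women are split. The article gives neither u nor k. Taking u = 3, the type 1 count, as an assumption:

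| assumed k | inside the root | SE inflation |
|---|---|---|
| 1.5 | 63.75/60 = 1.0625 | 3.1% |
| 3 | 84/60 = 1.40 | 18% |
| 5 | 132/60 = 2.20 | 48% |

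**3. Cost of leaving them out.** sqrt(60/57) = 1.026, an increase of 2.6%. At k = 1.5 inclusion and exclusion are about equal in precision. At k = 1 exclusion is a small net loss. Above 1.5 exclusion gains precision.

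**4. Precision in women without diabetes.** Between 24 + 21 = 45 and 26 + 22 = 48 women remain. The detectable difference at 80% power (two-sided 0.05 assumed, since the article states no alpha) is (1.960 + 0.842)·sqrt(1/n1 + 1/n2) in SD units:
- 30 vs 30: 0.72 SD
- 26 vs 22: 0.81 SD
- 24 vs 21: 0.84 SD

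**5. Is the diabetes imbalance established?** Fisher's exact test gives p = 0.33 for 4 vs 8 of 30 and p = 0.55 for 6 vs 9 of 30.

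**The case against.** The strongest reply is that a journal article condenses the plan, and that analysis sets for single laboratory outcomes belong in a statistical analysis plan that is not shown. That plan could well contain such a rule. But the article goes further than silence: it fixes one model and its terms for all physiological outcomes, alongside a baseline table that already shows the diabetes mix. Followed as written, that model includes the insulin users.

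Second, the article reports no insulin use and does not describe the insulin assay. This stands. Insulin use is very likely in women with type 1 diabetes, if the reported type is right, but it is an inference, and the size of the effect is unknown.

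Third, the model checks include heterogeneity of variance in subgroups, with age and BMI category given only as examples. Such a check could detect the extra variance, but diabetes is not named, no consequence is stated, and a variance check does not make the measurement comparable.

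A reader might also infer more than the document supports:
- *That change in glucose and glycated hemoglobin is largely a treatment artefact.* The comparison of interest is change over 22 weeks, so stable treatment largely cancels. Change in glycemic control among women with diabetes may itself be part of the response under study. Restricting these outcomes to women without diabetes would change the estimand.
- *That an uneven split biases the contrasts.* The imbalance is compatible with chance. It could still confound, since the cohorts are not randomized, but no direction or size of bias in change is shown. Type 1, the group most plausibly on insulin, is 2 vs 1.
- *That precision is badly damaged.* The large inflation figures come from assumed SD ratios of 3 to 5. A ratio of 1.5 gives about 3%.

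**Conclusion.** The point holds for fasting insulin. As stated, the analysis places values from probable insulin users into a named secondary outcome, where they do not measure what they measure in the other women. The loss of precision lies anywhere from about 3% to 48% in the standard error, under the assumptions of 3 affected women and change-SD ratios of 1.5 to 5. The gain from exclusion may therefore be small. The case for it rests mainly on what is being measured, and it costs only about 3%.

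For glucose, glycated hemoglobin and allostatic load, the document supports a sensitivity analysis and no more. The primary outcome, body weight, is not touched by this point.

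**What to change.** In Planned Statistical Analysis, state that every analysis of fasting insulin, including the aim 2 analyses that use it, leaves out women recorded as using insulin in the screening medication inventory. The data are already scheduled. Because the inventory is not repeated, insulin started during follow-up would not be identified from it; this should be stated as a limitation.

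As a sensitivity analysis only, show the cohort contrasts for glucose, glycated hemoglobin and the allostatic load score also in women without diabetes. Keep the all-women result as the main one. Do not make interpretation conditional on the two agreeing: with 45 to 48 women the results may differ through lost precision alone.

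The cost is that a few women leave the insulin analysis and one extra run is needed for the sensitivity contrasts. No new data collection is required.

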**Type 2 diabetes, n/N (%)**				
	Yes	4/30 (13)	8/30 (27)	12/60 (20)
	No	26/30 (87)	22/30 (73)	48/60 (80)
**High blood pressure, n/N (%)**				
	Yes	13/27 (48)	12/28 (43)	25/55 (45)
	No	14/27 (52)	16/28 (57)	30/55 (55)
**High cholesterol level, n/N (%)**				
	Yes	9/26 (35)	4/28 (14)	13/54 (24)
	No	17/26 (65)	24/28 (86)	41/54 (76)

^a^GED: General Educational Development Test.

^b^CPK: creatine phosphokinase.

^c^ALT: alanine transaminase.

^d^ALK: alkaline phosphatase.

## Discussion

### Summary

The RESPONSES study is investigating the association between food insecurity and obesity in African American women by measuring the episodic nature of food insecurity, related stress, and the role of psychological and physiological mechanisms. We have completed participant enrollment with 60 African American women (food-insecure cohort: n=30, 50%; food-secure cohort: n=30, 50%). The mean age of participants at enrollment was almost 47 (SD 10.8) years, and they had a mean BMI of 39.6 (SD 5.31) kg/m^2^. Once data collection is complete by the end of 2023, we will fulfill the study aims to (1) longitudinally assess body weight in addition to psychological and physiological parameters in food-insecure and food-secure African American women with obesity, to test our hypothesis that food-insecure African American women with obesity will demonstrate increased body weight and changes in psychological and physiological parameters consistent with elevated stress compared with food-secure African American women with obesity; (2) examine associations between changes in body weight and psychological and physiological parameters in food-insecure and food-secure African American women with obesity; and (3) longitudinally examine cyclic patterns in body weight, food insecurity, and stress in food-insecure and food-secure African American women with obesity and carry out a mediation analysis using the results from the psychological questionnaires.

The significance of the RESPONSES study is evidenced by a number of factors, including (1) an explicit focus on health disparities driven by both sex and race or ethnicity as evidenced in African American women, who experience a greater prevalence of both food insecurity and obesity; (2) the assessment of episodic food insecurity via longitudinal observational data collection; and (3) the triangulation of body weight and psychological and physiological parameters in the context of episodic food insecurity as a stressor. These points of significance directly relate to the *Strategic Plan for NIH Nutrition Research* by addressing the multiple recommendations highlighted in the position paper on food insecurity and obesity by Brown et al [90]. This study explicitly acknowledges the *episodic nature* of food insecurity by using a longitudinal study design to examine how the cyclic nature of food insecurity relates to body weight. Furthermore, this study will investigate the mechanisms underlying the linkage between food insecurity and obesity by focusing on a range of relevant psychological and physiological factors. Examining the interplay between psychological and physiological factors may be important to understanding the disparate rates of obesity-related comorbidities (eg, diabetes and hypertension) in African American women. Finally, the results from the RESPONSES study will hold important considerations for the assessment of body weight and psychological and physiological parameters in studies, wherein the assessment of these markers might need to consider corresponding episodes of food insecurity.

The RESPONSES study uses a longitudinal observational cohort design. Given the study objective, it is important not to intervene; thus, this study would not be possible with a randomized controlled trial design. Interventions should occur after a thorough understanding of the episodic nature of food insecurity and its impact on body weight and psychological and physiological processes. We recognize that only screening for dietary quality and not obtaining food intake data are study limitations, but this aspect of food insecurity (ie, energy-dense and nutrient-poor diet) is very well established in the literature, and body weight can serve as a proxy for food intake [19,20,91]. We are also measuring more tertiary constructs (eg, physical activity) that could be measured via more rigorous methods in future studies, such as energy intake via dietary recall or food pictures and energy expenditure via metabolic chamber or other methodology (eg, doubly labeled water and metabolic cart) to better assess energy metabolism.

